### Statistics

Comparisons between study arms will be by independent two-sample *t* tests or appropriate nonparametric equivalents using the prespecified comparisons.

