### Trial Design

A randomized trial design will be used for this evaluation with GP practices randomly assigned to one of the two arms described. We will notify clinicians of the STBD package and evaluation through primary care management, training forums, and communications. If interested, the practices will be able to opt in to the STBD evaluation via email. Once a practice has expressed interest, they will then be randomized to one of the two arms and either receive immediate access to the Internet-based training and print materials or receive access 4 months later (with awareness that their referral rates will be monitored).

The inclusion criteria for participants requires that they be GP practices in NHS Greater Glasgow and Clyde that have a contract for local enhanced services for long-term conditions (ie, diabetes) and have a unique clinical database (ie, not shared with another practice). Practices classified as “17c” (those with a separate NHS contract for long-term conditions) and those practices with a database shared with another practice (8 practices in area) are excluded.

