### Identification of Participants and Consent

As this is an evaluation study of a voluntary training program offered to GP practices as part of the usual program of NHS Health Improvement training, individual consent will not be required. By logging in to the Internet-based training website, practices will be agreeing to participate in the evaluation of the effectiveness of the training. No practices, staff, or patients will be identified during the evaluation. This information is in the letter instructing practices how to log into the training website. Patient data will be used to evaluate the outcomes of the training program, but this will be at the level of the intervention (ie, by GP practice) using health record linkage. The patient data and practice ID will be anonymized and accessed via the NHS Greater Glasgow and Clyde IT Safe Haven, so no individual patient consent will be sought.

All practices will be informed about the available training via communications from clinical directors and other routine NHS communication sources, which will explain the purpose of STBD and provide contact details to use if they are interested in completing the training. Those practices that do opt in will be randomized to one of the two arms of the evaluation. Practices gaining immediate access to the Internet-based training will be emailed with instructions on how to access the site (Arm 1). They will also be sent a practice kit containing the print materials designed to support implementation of STBD within their practice. Those practices randomized to Arm 1 will be sent options for the supplementary face-to-face training sessions and instructions on how to book a place through NHS Greater Glasgow and Clyde Health Improvement. Practices that express an interest and are randomized to Arm 2 (ie, delayed access to the STBD training), will be notified by email that their instructions for access will be available in 4 months. They will be made aware that their referral data over the next 4 months will be analyzed as part of the evaluation. A reminder letter/email/ phone call will be sent/made to any practice that opts in and does not access or complete the Internet-based training module after 4 weeks.

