### Randomization

Practices will be randomized to immediate or delayed intervention using the Internet-based random allocation software (Castor Electronic Data Capture) using permuted random block sizes of 4.

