### Outcome Measures

The primary outcome is change in primary care referral rate to an adult NHS weight management service. Using data from the weight management database held by NHS Greater Glasgow and Clyde, the ratio of referrals over 3 months before and after the STBD intervention (allowing 1 month for completion) will be calculated. Secondary outcome measures include change in referral, including uptake ratio, local enhanced service template completion (weight management discussed); change in local enhanced service template completion; completion of lifestyle weight management phase (completion defined as 80% attendance); weight change (kg and %) in lifestyle weight management phase for those attending >1 session; and weight change (kg and %) at 1 year for all patients (data from annual diabetes review). Tertiary outcomes include diabetes medications at time of referral, that is percentage on weight gaining medications (sulphonylureas, thiazolidinediones, insulin), and percentage on weight neutral/reducing medications (GLP-1 agonists, metformin, DPP-IV inhibitors, SGLT2 inhibitors). Exploratory analyses (before and after) will be carried out to look at the effect of completion of training; change in referral rate analysis of those who completed Internet-based training only; when training done was completed by GP only, by practice nurse only or both; and change in referral rate in those where one practice member completed Internet-based plus face-to-face training.

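### Practices are randomised, but Textbox 1 calls the trial individually randomised, and the single rule for between-arm tests makes no allowance for practice in patient-measured outcomes

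*Protocol article*

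**What the plan says.** The unit of randomisation is stated consistently in the body of the article. Trial Design has "GP practices randomly assigned to one of the two arms described", and Randomization has "Practices will be randomized to immediate or delayed intervention", in permuted blocks of 4. The Abstract and Data Handling agree. The PICOS summary in Textbox 1 lists practices as the participants but gives the study design as individually randomised.

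The Statistics section is a single sentence: "Comparisons between study arms will be by independent two-sample" *t* tests "or appropriate nonparametric equivalents using the prespecified comparisons". It does not distinguish one kind of outcome from another.

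Outcome Measures contains both kinds:

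- **By practice.** For the primary outcome, "the ratio of referrals over 3 months before and after the STBD intervention (allowing 1 month for completion) will be calculated". This is naturally one value per practice.
- **On patients.** Weight change in the lifestyle phase among attenders, weight change at one year, completion of the lifestyle phase (80% attendance) and diabetes medication class at referral.

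On the level at which patient data are used, the section on identification and consent says that "this will be at the level of the intervention (ie, by GP practice) using health record linkage". Neither Outcome Measures nor Statistics turns this into a unit of analysis.

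**The concern.** When practices are randomised, patients in one practice share its clinicians and its allocation, so their outcomes tend to be correlated. A two-sample *t* test and its rank-based counterpart both assume independent observations. Applied to individual patients, they give confidence intervals that are too narrow and too many false positives on the weight, completion and medication outcomes.

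The label adds to the risk. An analyst or meta-analyst who takes the design from Textbox 1 would see no reason to allow for practice.

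Reading the rule as a test on practice means removes the false-positive problem but leaves a smaller one. A practice with one referred patient counts as much as a practice with many, and a practice with none has no mean to enter.

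**Working it through.** **1. The plan's own figure.** Sample Size gives 80 per group for 80% power, a difference of 0.5 and an SD of 1.12. Alpha is not stated; 0.05 two-sided is assumed.

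n = 2 × (1.96 + 0.84)² × 1.12² / 0.5² ≈ 79 per group by the normal approximation, and 79.7 (so 80) by the *t* distribution. A one-sided test would give 63, which does not match. The figure therefore reproduces with independent units and no design effect. That is appropriate when the unit is the practice and the outcome is one referral ratio per practice.

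**2. Patients per practice.** Two scenarios follow from the article:

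- *Referred patients:* 15 referrals in the 3 months after training in the feasibility study, read as the total over five practices. 15/5 = 3.
- *Upper scenario:* all patients in the area with type 2 diabetes and BMI of at least 30 (Introduction), over the 260 practices in the area (Discussion), assumed evenly spread. 25,109/260 = 96.6, about 97.

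**3. Patients treated as independent.** The article gives no ICC, so 0.01 to 0.05 is an assumption. With m patients per practice:

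- design effect DE = 1 + (m − 1) × ICC
- standard error too small by a factor of √DE
- true alpha = 2 × (1 − Φ(1.96/√DE))

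The last two columns are simulated rejection rates under no effect, with 50 practices per arm and 4,000 runs per row.

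| m | ICC | DE | √DE | True alpha | Simulated, patients as units | Simulated, one mean per practice |
|---|---|---|---|---|---|---|
| 3 | 0.01 | 1 + 2 × 0.01 = 1.02 | 1.01 | 0.052 | 0.052 | 0.050 |
| 3 | 0.05 | 1 + 2 × 0.05 = 1.10 | 1.05 | 0.062 | 0.061 | 0.047 |
| 97 | 0.01 | 1 + 96 × 0.01 = 1.96 | 1.40 | 0.16 | 0.157 | 0.054 |
| 97 | 0.05 | 1 + 96 × 0.05 = 5.80 | 2.41 | 0.42 | 0.410 | 0.049 |

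The same *t* test is valid in the last column and invalid in the one before it when m is large. The choice of unit decides this, not the test itself.

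**4. Practice means with few patients.** The Introduction reports that 1537 of 5855 referred patients attended assessment: 1537/5855 = 0.26. At 3 referrals per practice that is 3 × 0.26 ≈ 0.8 attenders per practice in 3 months. If the counts were Poisson with that mean (an assumption), exp(−0.79) ≈ 0.45, so about 45% of practices would have no attender and no mean for lifestyle-phase weight change. In the feasibility study, two of five practices made no referrals in the period just before training, so empty practices are realistic.

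**The case against.** The strongest reply is that the article already names the right level. It says that patient data are used by GP practice. Together with the Statistics sentence, this describes two-sample tests on practice values, a valid analysis of a cluster trial that held its error rate in all four simulated settings. Nothing in the article says that patients will be analysed as independent observations. Several outcomes are also worded as ratios, changes or percentages, which suit practice summaries.

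Much of this stands, and it rules out three stronger readings that a reader might infer:

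- *That every comparison is invalid.* The primary outcome is unaffected, and so is any analysis with one value per practice. The plan is also not confined to the *t* test, although the nonparametric option assumes independence too.
- *That the trial will have false-positive rates of 16 to 42%.* This needs patients as the unit, an assumed ICC and about 97 patients per practice. The Discussion describes the weight and medication outcomes as those of referred patients, which points to the small-cluster scenario.
- *That practice means would also inflate error.* They do not. Equal weighting costs efficiency and information.

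The reply does not settle the matter. The statement on practice level explains why individual consent is not sought; it is not an analysis rule. One-year weight change is defined for all patients, without a clear limit to those referred.

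It can also be said that no reader of the Methods would mistake what was randomised, and that model details belong in an SAP that is not shown. Both are fair. The label is nevertheless wrong where it stands, and the article does state a single rule for all outcomes.

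**Conclusion.** The point holds as a wrong design label and an analysis rule that is too general for the outcomes it covers. It does not touch the primary comparison.

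For patient-measured secondary and tertiary outcomes, the size depends on the unused choice of unit. If patients are the unit, true alpha is about 0.05 to 0.06 at 3 referred patients per practice, which is minor. The 0.16 to 0.42 range is an upper bound that applies only if one-year weight change covers every eligible patient in the practice. Both ranges rest on the assumed ICC of 0.01 to 0.05 and on equal practice sizes. If practices are the unit, the error rate holds; what is lost is efficiency and the practices with no patients.

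**What to change.** 1. In Textbox 1, give the study design as *cluster-randomised (by practice)*.
2. In Statistics, limit the *t* test or nonparametric test to outcomes with one value per practice, including the primary outcome.
3. For outcomes measured on patients, name a mixed model or GEE with practice as the cluster, and adjust the weight outcomes for baseline weight. Such a model weights practices by the information they carry. It cannot supply data for a practice with no patients, so the report should say how many practices per arm contribute to each outcome.

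The cost is a few changed sentences and slightly more analysis work with standard software. Confidence intervals will be wider than those from a patient-level *t* test.

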### Trial Schedule

The schedule and timeline for the trial are outlined in Table 2.

**Table 2 table2:** Trial schedule and timeline.

Activity	Owner	Outcome	Estimated timeline
Ad placed within primary care communication channels and forums	University of Glasgow and NHS^a^ Greater Glasgow and Clyde	Notify practice of training. Opt-in of practices to evaluation	Oct 2017
Randomization	University of Glasgow	Randomized practices that opt in to Arm 1 or 2 using Castor Electronic Data Capture	Oct 2017-Apr 2018
Practices notified of arm for evaluation	University of Glasgow	Practices informed if they are immediate or delayed access to training by email	Oct 2017-Apr 2018
Arm 1: Practices sent patient materials, posters, and invited to complete Internet-based training with or without face-to-face training	NHS Greater Glasgow and Clyde Health Improvement	Practices randomized to Arm 1 or 2 invited to complete training	Oct 2017-May 2018
Notification of completion of Internet-based training (Arm 1)	University of Glasgow	Website analytics notifies research team of Internet-based training completion by practice code	Oct 2017-Sept 2018
Reminder notice/phone call	University of Glasgow	Practices not having completed the Internet-based training will be sent a reminder and also the practice will be phoned once	Nov 2017-May 2018
Provision of face-to-face training (Arm 1)	NHS Greater Glasgow and Clyde Health Improvement	Notification of attendees provided to NHS team	A study-specific face-to-face training session available every 2 months Oct 2017-Jun 2018
Access to referral data	NHS Safe Haven	Statistician has remote access to anonymized data via a virtual private network	Oct 2018
Comparison of change in referral rate (Arms 1 vs 2)	Statistician	Report of results	Dec 2018

^a^NHS: National Health Service.

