### Data Handling

We have prepared a custom electronic case report form for the purposes of randomizing the practices to immediate or delayed access to STBD training at the point of opting in. The remaining data for use in this evaluation will be from routine health records (ie, weight management and diabetes care). Access to these data will be via the NHS Greater Glasgow and Clyde Safe Haven (already approved by the Local Privacy Advisory Committee). The data will be fully anonymized and accessed via a virtual private network. Access will be only for the duration of the analysis of the data for the evaluation.

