## Results

The first invitations for this evaluation were emailed in October 2017. Recruitment for this trial closed in April 2018. As there was an extremely large response to the single invitation email from the Primary Care Diabetes Lead sent in March 2018, to avoid discouraging willing practices we decided to extend the trial to include 100 practices (50 per arm). Follow-up is ongoing and linkage of practice data with referral data was completed by October 2018. It is expected that the trial will report in early 2019.

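### The stated two-sample test has no term for randomisation period, so it may be slightly conservative: allocation is blocked in time and the outcome windows roll with entry.

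*Protocol article*

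**What the plan says.** All places are in the protocol article.

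- **Randomization:** allocation is done "using permuted random block sizes of 4", with no stratification factor named.
- **Data Handling:** the electronic form serves for "randomizing the practices to immediate or delayed access to STBD training at the point of opting in", so blocks fill in time order.
- **Trial Schedule, Table 2:** randomisation runs "Oct 2017-Apr 2018".
- **Outcome Measures:** for the primary outcome, "the ratio of referrals over 3 months before and after the STBD intervention (allowing 1 month for completion) will be calculated".
- **Identification of Participants and Consent:** delayed-access practices are told that "their referral data over the next 4 months will be analyzed as part of the evaluation". That matches one month for completion plus a three-month after window, counted from notification.
- **Results:** entry was uneven in time, with an "extremely large response to the single invitation email from the Primary Care Diabetes Lead sent in March 2018".
- **Statistics:** "Comparisons between study arms will be by independent two-sample" t tests, or suitable nonparametric equivalents. No block or period term appears.

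**The concern.** The windows fall in different seasons for different practices. On the natural reading that the clock starts at randomisation, a practice entering on 1 October 2017 compares July-September with November-January. One entering on 1 April 2018 compares January-March with May-July. The expected ratio can therefore differ by entry date for reasons unrelated to the training. Entry date also separates early volunteers from practices that answered the March 2018 email.

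Time-ordered blocks spread this variation evenly over the arms, so it largely cancels from the difference in means. The plain t test, or an unstratified rank test, still counts it as noise. At stake is precision only, in a trial with 50 practices per arm.

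**Working it through.** **1. The plan's own figure.** Inputs from Sample Size: difference 0.5, hypothetical SD 1.12, power 80%. A two-sided 5% level is assumed, as none is stated.

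n per group = 2 × (1.960 + 0.842)² × 1.12² / 0.5² = 78.8, so 79. The t-based solution is 79.7, so 80, as stated.

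**2. The stated test at the actual size.** With 50 per arm (Results), SE = 1.12 × √(2/50) = 0.224. The 95% half-width is 1.984 × 0.224 = 0.444. Power for 0.5 is about 0.60.

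**3. Effect of leaving period out.** Let r be the share of outcome variance lying between blocks or periods. Each block of 4 has two practices per arm, so that share cancels from the difference:

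- true variance of the difference = (4/100) × σ² × (1 − r)
- variance the t test estimates ≈ (4/100) × σ²
- SE ratio ≈ 1/√(1 − r)

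A simulation of 25 blocks of 4 (total SD 1.12) compared the plain t test (98 df) with full block adjustment (74 df):

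| r (assumed) | 1/√(1 − r) | Half-width, plain / adjusted | Type I error, plain | Power, plain / adjusted |
|---|---|---|---|---|
| 0 | 1.000 | 0.443 / 0.445 | 0.050 | 0.60 / 0.60 |
| 0.02 | 1.010 | 0.443 / 0.440 | 0.049 | 0.60 / 0.61 |
| 0.05 | 1.026 | 0.443 / 0.433 | 0.044 | 0.60 / 0.62 |

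**4. What r is plausible.** The documents do not give it. The feasibility study reports 8 and 10 referrals in its two pre-training quarters from five practices, which is 1.6 to 2.0 per practice per quarter. Counting noise is therefore large.

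Poisson counts were simulated with mean 2 or 4 per quarter and entry over seven months, either even or with a late surge. An assumed annual cycle peaked at the start of October, and 0.5 was added to each count so that the ratio is always defined. The excess SE of the plain test on the ratio scale, even entry / late surge, was:

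| Peak-to-trough ratio (assumed) | Mean 2 per quarter | Mean 4 per quarter |
|---|---|---|
| 1.25 | 0.3% / 0.4% | 0.5% / 0.6% |
| 1.5 | 1.1% / 1.0% | 1.8% / 1.5% |
| 2.0 | 2.9% / 2.4% | 5.1% / 3.3% |

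The log ratio gives somewhat more, up to about 7% in the last cell. With three period terms in place of 24 block terms, and taking both scales, the plain intervals are about 0.2-2% too wide for ratios of 1.25 to 1.5 and about 2-6% for 2.0.

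The timing of the peak is also an assumption. Moving it through the year, with a peak-to-trough ratio of 2.0 and three period terms, gave about 0.4% to 5% on the ratio scale at mean 2, and up to about 7.5% at mean 4. On the log scale, which the plan does not name, the least favourable timing goes higher.

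**5. Cost if period has no effect.** The t quantile rises from 1.9845 (98 df) to 1.9855 (94 df, four period terms), or 0.05%. Simulated intervals were no more than about 0.1-0.2% wider.

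**The case against.** **A plain comparison after unstratified blocking is common and valid.** This stands. There is no bias and no inflated type I error. The point is a refinement that costs almost nothing.

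**Adjustment terms belong in the analysis plan.** This stands in part. The Statistics section is one sentence, and a fuller plan may adjust. But the sentence names a method, and that method does not follow the allocation. If the fuller plan already adjusts, the two texts only need to be aligned.

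**Nothing in the documents shows seasonality.** This stands. The two pre-training quarters give 10/8 = 1.25 from five practices. A difference of 2 against a Poisson SE of √18 = 4.2 is well within chance.

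A reader might infer that the intervals are certainly too wide, or that 10-20% of the variance is recoverable, with power rising to around 70%. The documents support neither. With r = 0 the intervals are not too wide, and counting noise at these referral numbers makes shares that large unlikely. Nor should this be confused with the loss of power from about 0.80 at 80 per group to about 0.60 at 50, which is larger and separate.

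The arithmetic covers the t test only. No size is claimed for the rank test.

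**Conclusion.** The point holds as a conditional one. The stated test omits a factor that the allocation balances and on which the outcome windows depend. If that factor matters, the test is conservative: intervals roughly 0-6% too wide, mostly under 4%, with a gain of one or two percentage points of power at r of 0.02 to 0.05.

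The range rests on assumed referral counts of 2 to 4 per quarter, seasonal peak-to-trough ratios of 1.25 to 2.0, an assumed timing of the peak, and windows counted from entry. The case for change is that the downside is negligible, not that the loss is large.

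**What to change.** In Statistics, prespecify for the primary and other practice-level outcomes a linear model with arm plus randomisation period as a fixed effect. Define a few calendar periods before the outcome data are seen. Keep each block of 4 whole within a period, and place one cut at the March 2018 email. List the cut dates so that the choice is not left to the analyst.

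If a rank test is used, stratify it by the same periods (van Elteren) or use a permutation test within blocks.

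The change takes a sentence or two and 1 to 4 degrees of freedom. It needs no new data, since allocation runs through the electronic randomisation system, which should hold the dates.

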### Study Closure

The evaluation will end 15 months after the practices are invited to participate, to allow time for training, changes in practice, and patient attendance at services.

